### Assignment of interventions: Blinding

This study will be conducted as a participant- and assessor-blinded randomized controlled trial. Participants will be informed that they are receiving training, but will not know whether the program includes neuromuscular training with or without cognitive components. Given the structural similarity between protocols, participants may be unlikely to determine their group assignment. To minimize communication between groups, intervention and control sessions will be scheduled on separate training days. Outcome assessors will remain blinded to group assignments. Participants will be instructed not to disclose intervention-related information during evaluations.

### Data collection methods

To evaluate landing kinematics, electrocortical brain activity, and muscle activity, a single-leg landing test will be administered under two experimental conditions: with and without a concurrent cognitive task. After reflective markers and EMG sensors are placed on the participant’s preferred kicking leg (determined using a ball-kicking test) and the EEG cap is fitted, participants will perform the landing test three times with cognitive load and three times without cognitive load. During the test, frontal-plane knee valgus and sagittal-plane knee flexion angles, as well as trunk flexion and lateral flexion angles, will be captured using two cameras positioned for anterior and lateral views. Muscle activity in the vastus medialis, vastus lateralis, biceps femoris, semitendinosus, and gluteus medius will be measured using surface EMG. Electrocortical brain activity will be recorded via 19 EEG channels at theta and alpha-2 frequency bands [25].

To begin the test, participants will cross their arms over their chest to minimize upper-limb movement while standing on a 30 cm-high step [22]. The heel of the dominant foot will be positioned at the edge of the step to limit preparatory movement. Participants will look forward to a wall-mounted screen. After the presentation of the final arrow cue, the participant will perform a single-leg landing on either the right or left target area marked on the floor, based on the direction of the final arrow. The test will also be conducted without cognitive load as a control condition. If the participant cannot maintain balance or demonstrates loss of control (for example, requires additional support, steps outside the target area, or loses postural stability), the trial will be considered invalid and excluded from analysis [26].

After completing the landing tests, participants will stand on a foot scan platform to perform a 30-second balance assessment under eyes-open and eyes-closed conditions. Subsequently, knee muscle strength (flexors and extensors) and hip muscle strength (abductors and adductors) will be measured using a hand-held dynamometer [17]. Knee joint proprioception at 60° of flexion (non-weight-bearing) will be assessed using a goniometer.

In addition, health-related quality of life will be evaluated before and after the intervention using the SF-12 questionnaire [27]. The analysis criterion for all variables will be the change from baseline values.

### Data management

Two trained sports rehabilitation specialists will collect and enter all data electronically using secure, password-protected software. Each participant will receive a unique identification number to ensure anonymity. The principal investigator (PI), in collaboration with the data management and analysis team, will perform data quality control, checking for missing values, out-of-range entries, and duplicate records. This team will operate separately from the intervention delivery team to minimize potential bias and ensure data integrity, adherence to pre-specified statistical procedures, and reproducibility.

### Statistical methods

Descriptive statistics, including means and standard deviations, will summarize the data. The Shapiro-Wilk test will assess data normality. Baseline characteristics will be summarized descriptively between groups. Repeated-measures ANOVA will be used to evaluate the group × time interaction effect as the primary indicator of intervention effectiveness (training vs. control; pre-test vs. post-test). Pairwise comparisons following significant interactions will be conducted with Bonferroni correction to control type I error. The five secondary outcome domains (cortical brain activity, lower-limb muscle activation, single-leg balance, muscle strength, and knee joint proprioception) will be interpreted as exploratory outcomes and hypothesis-generating findings. Partial eta squared will quantify effect sizes, interpreted as small (0.01), medium (0.06), or large (0.14). All analyses will be performed using SPSS version 27 with α = 0.05 and a 95% confidence level.

Given the modest sample size, supplementary analyses will be conducted. Baseline values will be reviewed descriptively, and if clinically meaningful baseline imbalance is observed, ANCOVA models adjusting for baseline values will be performed as sensitivity analyses. Missing data patterns will be assessed, and linear mixed models with appropriate covariance structures will be considered as sensitivity analyses to evaluate robustness under missing-at-random assumptions. Any meaningful discrepancy between supplementary analyses and the primary ANOVA will be reported and discussed.

To assess clinical significance and intervention effectiveness, minimal clinically important difference (MCID) and minimal detectable change (MDC) will be calculated at a 95% confidence level. The MDC will be derived using the standard error of measurement (SEM), as defined by the following formulas [28]:

$$\begin{array}{c} \text{SEM }=\;{\text{SD}}_{\text{pre}}\;\times \;\sqrt{(\text{1}-\text{ ICC})\;} \end{array}$$

$$\begin{array}{c} {\text{MDC}}_{\%\text{9}\text{5}}\;=\;\text{1}.\text{96 }\times \sqrt{\text{2}\;\times \text{ SEM}} \end{array}$$

$$\begin{array}{c} {\text{MCID}}_{\text{RCI}}=\;\text{1}.\text{96 }\times \;{\text{SD}}_{\text{pre}}\;[\sqrt{\left(\text{2}\times (\text{1}-\text{ICC})\right)}] \end{array}$$

The reliable change index (RCI) will be calculated to determine whether observed changes exceed measurement error. In these equations, SDpre denotes the standard deviation of pre-test scores in the training group, and ICC denotes the intraclass correlation coefficient (test-retest reliability). MCID_RCI_ will be used to determine the minimum clinically significant change. Reliability coefficients from previously reported studies in comparable populations will be used.

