**Methods:**

This study protocol describes a two-arm, parallel-group randomized controlled trial that will assess an eight-week neuromuscular-cognitive training program for female volleyball players aged 18–23 with clinically confirmed DKV and competitive experience. Participants will be randomly assigned to either an experimental group that will receive integrated neuromuscular-cognitive training or a control group that will receive standard neuromuscular training without cognitive components. The intervention will combine sport-specific motor tasks with cognitive challenges aimed at improving neuromuscular control and decision-making during dynamic movements. The primary outcome will be single-leg landing kinematics under cognitive and non-cognitive conditions. Secondary outcomes will include cortical brain activity, lower limb muscle activation, single-leg balance, muscle strength, and knee joint proprioception. Additional measures will involve participant feedback on training intensity and satisfaction.

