**Discussion:**

If effective, this protocol will provide evidence for integrating cognitive training into ACL injury prevention programs for female volleyball athletes. By examining the interaction between cognitive load and neuromuscular control under sport-specific conditions, this study may contribute to a better understanding of cognitive and neuromuscular mechanisms involved in injury prevention and inform future preventive strategies in sports medicine.

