In real-game situations, jumping and landing occur under cognitively demanding and unpredictable conditions, requiring rapid decision-making, simultaneous processing of multiple stimuli, and swift motor responses [13]. This phenomenon, known as cognitive-motor interference or dual-task interference, occurs when cognitive demands compete with motor control for limited attentional resources. Cognitive challenges may impair the regulation of complex motor tasks, such as landing, and exacerbate movement deficiencies like DKV [13–16].

However, most existing injury prevention programs, such as FIFA 11+ and the PEP program, primarily focus on physical components, including muscle strengthening, balance training, and landing technique modification, while providing limited emphasis on cognitive domains such as attention, decision-making, and motor planning [17]. As a result, their applicability to cognitively demanding competitive environments may be limited. Thus, a training protocol that integrates neuromuscular performance and cognitive processing offers a potentially valuable approach to reducing ACL injury risk in female volleyball players, particularly those with DKV. Therefore, this study protocol addresses this gap by describing a randomized controlled trial designed to evaluate a neuromuscular-cognitive training program specifically developed for female volleyball athletes.

The primary objective of this trial will be to evaluate the effects of an eight-week neuromuscular-cognitive training protocol on single-leg landing mechanics, specifically peak knee valgus angle and frontal plane projection angle, during dual-task cognitive conditions in female volleyball players with DKV. The secondary objectives will be to assess the protocol’s effects on cortical brain activity patterns during motor tasks, measured by EEG, lower extremity muscle activation patterns during landing, assessed by surface electromyography (EMG), single-leg balance performance under both static and dynamic conditions, lower limb muscle strength (quadriceps, hamstrings, and hip abductors), and knee joint proprioception. Finally, this trial aims to contribute evidence regarding whether integrating cognitive challenges into neuromuscular training results in different outcomes compared with standard neuromuscular training alone, thereby informing future ACL injury prevention strategies in this high-risk athletic population.

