### Outcomes

Participants will first receive detailed information about the study procedures, ethical considerations, and potential risks before providing informed consent and completing a personal information form. They will then undergo standardized instructions and a familiarization session, followed by a warm-up to standardize physical readiness and minimize injury risk. Assessments will be conducted 72 hours before the start of the eight-week neuromuscular-cognitive training protocol (pre-test) and within 72 hours after the final session (post-test) to evaluate its effects on modifiable ACL injury-related risk factors in female volleyball players with DKV. All assessments will take place in the Sports Rehabilitation Laboratory at Bu-Ali Sina University under standardized temporal and environmental conditions, with precise measures to control external variables and ensure accurate evaluation.

The primary outcome is the change in two-dimensional landing kinematics, particularly movement patterns associated with DKV, during single-leg landing under two conditions: with and without a concurrent cognitive task. Secondary outcomes include electrocortical brain activity measured by electroencephalography (EEG), lower limb muscle activity assessed by surface electromyography (sEMG), single-leg balance, lower limb muscle strength, and knee joint proprioception. These measures will determine the intervention’s impact on neuromuscular, cognitive, and biomechanical factors associated with ACL injury risk.

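### The primary group × time test is not tied to a landing condition and has no condition term, so a conclusion that the benefit is specific to cognitive load has no planned test

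*Protocol article*

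**What the plan says.** **Objective.** The Background sets the primary objective on landing mechanics, "specifically peak knee valgus angle and frontal plane projection angle, during dual-task cognitive conditions in female volleyball players with DKV". That is the loaded condition alone.

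**Outcome.** The abstract's Methods paragraph makes both conditions primary: "The primary outcome will be single-leg landing kinematics under cognitive and non-cognitive conditions". The Outcomes section agrees, defining the primary outcome as change in landing kinematics "during single-leg landing under two conditions: with and without a concurrent cognitive task".

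**Data.** Under Data collection methods, "participants will perform the landing test three times with cognitive load and three times without cognitive load". The same section gives the unloaded landing its role: "The test will also be conducted without cognitive load as a control condition".

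**Purpose.** The abstract's Discussion describes what the trial may contribute: "By examining the interaction between cognitive load and neuromuscular control under sport-specific conditions".

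**Test.** Under Statistical methods, "Repeated-measures ANOVA will be used to evaluate the group × time interaction effect as the primary indicator of intervention effectiveness". The factors are then listed in brackets as training versus control and pre-test versus post-test. Condition is not mentioned. The supplementary ANCOVA and mixed models deal with baseline imbalance and missing data, not with load.

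**The concern.** The outcome has three dimensions (arm, visit, condition) and the stated primary test has two. This leaves two gaps.

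First, the test is not tied to a condition. The Background points to loaded landings, whereas the abstract and the Outcomes section point to both. Statistical methods does not choose between them, and does not say whether the two are averaged, tested separately, or restricted to one.

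Second, no planned test uses the unloaded landings as a comparator, although they are collected as a control condition. Whether the training effect is larger under load is a group × time × condition question. A group × time test on loaded data, unloaded data or their mean does not address it.

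The introduction argues from dual-task interference, so a load-specific reading of the results will be attractive. Without a planned contrast, such a reading could rest on one condition reaching significance and the other not, which is weak evidence of a difference. If the conditions were averaged instead, a benefit confined to loaded landings would be diluted.

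**Working it through.** **Inputs from the Sample size section.** Partial η² = 0.19, f = 0.48, α = 0.05, power 0.95, r = 0.5 between repeated measures, minimum N = 18, enrolment 30, attrition 20%. Completers: 30 × 0.8 = 24, or 12 per arm.

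**Assumptions not in the documents.** The change-score SD is the same in both conditions. The correlation c between the two conditions' change scores is 0.3 to 0.8.

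**Step 1: reproduce N = 18.** For two groups and two visits the noncentrality is λ = f²·N·m/(1 − r), with m = 2 and df 1 and N − 2.
- N = 16: λ = 0.2304 × 16 × 2/0.5 = 14.75, power 0.946.
- N = 18: λ = 16.59, power 0.968.

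So 18 is the smallest even N that reaches 0.95. The figure reproduces for a group × time design with no condition factor.

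**Step 2: the effect in SDs of change.** Let δ be the between-arm difference in mean change divided by the SD of change. For N participants split equally, the squared noncentrality of the t-test is δ²N/4.
- Effect behind N = 18: δ²/4 = 0.2304 × 2/0.5 = 0.9216, so δ = 1.92.
- Partial η² = 0.19 taken directly for this 1-df term: δ²/4 = 0.19/0.81 = 0.2346, so δ = 2 × 0.484 = 0.97.

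The two readings differ by a factor of about two. Which is realistic is a separate sample-size question, so both are carried forward.

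**Step 3: effect present only under load, 24 completers.** The noncentrality is δ/(s·√(4/24)), where:
- loaded landings only: effect δ, s = 1;
- mean of both conditions: effect δ/2, s = √((1 + c)/2);
- loaded minus unloaded, which is the group × time × condition test: effect δ, s = √(2(1 − c)).

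Example for the mean at δ = 0.97 and c = 0.3: 0.4845/(0.806 × 0.408) = 1.47, power 0.29.

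| δ | c | Loaded only | Mean of both | Group × time × condition |
|---|---|---|---|---|
| 0.97 | 0.3 | 0.62 | 0.29 | 0.48 |
| 0.97 | 0.5 | 0.62 | 0.26 | 0.62 |
| 0.97 | 0.7 | 0.62 | 0.23 | 0.83 |
| 0.97 | 0.8 | 0.62 | 0.22 | 0.95 |
| 1.92 | 0.3 | 0.99 | 0.80 | 0.97 |
| 1.92 | 0.5 | 0.99 | 0.74 | 0.99 |
| 1.92 | 0.7 | 0.99 | 0.68 | >0.99 |
| 1.92 | 0.8 | 0.99 | 0.66 | >0.99 |

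**Step 4: equal effect in both conditions, tested separately (simulation, 24 completers).** Exactly one of the two tests is significant in 39% (c = 0.3), 32% (0.5), 25% (0.7) and 20% (0.8) of trials at δ = 0.97. Loaded significant and unloaded not makes up about half of these, 19% to 10% of trials. At δ = 1.92 the discordant share is about 1% throughout. The group × time × condition test rejects in 5% of trials, as it should when the effect does not differ by load.

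**The case against.** The strongest reply is that the two-factor test already answers the trial's question. Fitted to the loaded landings, group × time tests directly whether training changes landing under load, which is the Background objective, and needs no condition term. This stands. A reader might infer that the primary null is the wrong one; the documents do not support that.

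A reader might also infer that the plan will average the conditions, or will claim load-specificity from one significant and one non-significant result. Statistical methods states neither. Steps 3 and 4 show what the silence would allow, not what is planned.

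Third, load-specificity is not a listed objective. The trial's comparison is between arms, and a benefit equal in both conditions would satisfy it. The wording about an interaction with cognitive load comes from one sentence in the abstract's Discussion, which says only that the study may add to understanding. This also stands. It limits the point to a secondary contrast, needed if a load-specific conclusion is to be drawn.

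Fourth, the harm depends on the effect size. At the 1.92 SD behind N = 18, discordant significance is rare and averaging still leaves 66% to 80% power. That is correct, which is why both effect sizes are shown.

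Last, a condensed article may leave modelling detail to a statistical analysis plan. That does not dispose of the point: the article itself states the primary model and its factors, and these do not match the two-condition outcome it defines.

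**Conclusion.** The point holds in limited form. The primary test is not tied to one condition, and the sections that define the objective and the outcome do not agree on which it should be. On any reading, the stated model cannot show that the training effect differs by cognitive load, so a load-specific conclusion would have no planned test behind it.

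The practical cost depends on two things the documents do not settle: how the conditions enter the analysis, and how large the effect is. Under averaging, the loss for a load-only effect is 33 to 40 percentage points at 0.97 SD and 19 to 33 points at 1.92 SD. Under separate testing, misleading discordance is common at 0.97 SD and negligible at 1.92 SD. All these figures assume 12 completers per arm, equal change-score SDs and a between-condition correlation of 0.3 to 0.8. The change is worth making because the required data are already being collected; it does not imply that the trial cannot meet its primary objective.

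**What to change.** Three changes to Statistical methods, with the Outcomes section and abstract aligned to them:

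1. State that the primary group × time test is run on the loaded (dual-task) landings, in line with the Background objective.
2. Prespecify group × time × condition as the labelled secondary test for any load-specific claim. Equivalently, compute each athlete's dual-task cost (loaded minus unloaded valgus angle) at each visit, and report the between-arm difference in its change with a 95% CI.
3. State that a difference in significance between the two conditions will not be read as evidence of a load-specific effect.

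The cost is wording and one additional prespecified contrast. No new data are needed. At 0.97 SD, power for that contrast runs from 48% to 95% depending on the between-condition correlation, so a non-significant result should be reported with its interval and not as evidence that load makes no difference.

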### Screening procedures

All potential participants will complete two screening assessments in the Sports Rehabilitation Laboratory:

*1- Tuck Jump Test with Cognitive Task:* Participants will perform continuous tuck jumps for 10 seconds while responding to visual stimuli. The test will be video-recorded and assessed for neuromuscular deficits associated with DKV [21].

*2- Single-Leg Landing Task with Cognitive Task:* Participants will perform single-leg landings from a 30-cm box while completing a visual discrimination task. Landing mechanics will be captured using 2D motion analysis techniques to quantify knee valgus angles. DKV will be defined as a peak knee valgus angle greater than 12 degrees during the single-leg landing task, consistent with established thresholds for increased ACL injury risk [22].

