### Sample size

The sample size was calculated using G*Power software (version 3.1) for a repeated-measures ANOVA (within-between interaction) to detect changes in DKV angle at initial contact. The effect size was derived from the group × time interaction reported for DKV at initial contact in a previous neuromuscular training study with dual cognitive tasks [24] (partial η² = 0.19), converted to an effect size f = 0.48. Based on a significance level (α) of 0.05, statistical power (1-β) of 0.95, and an assumed correlation of r = 0.5 between repeated measures, a minimum total of 18 participants was required. The required sample size was initially determined based on the primary outcome measure (the DKV angle) to ensure sufficient statistical power. To adjust for multiple secondary outcome assessments and an estimated 20% attrition rate, we inflated the target enrollment to 30 participants, who will be randomly allocated in a 1:1 ratio to the intervention and control groups.

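### The primary test is a valid but less efficient change-score analysis; baseline-adjusted ANCOVA should be the unconditional primary model, not a sensitivity analysis triggered by an undefined imbalance

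*Protocol article*

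**What the plan says.** All of this is in the Protocol article.

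- **Primary test** (Statistical methods): "Repeated-measures ANOVA will be used to evaluate the group × time interaction effect as the primary indicator of intervention effectiveness", for the contrast "training vs. control; pre-test vs. post-test". There are two arms and two assessment times.
- **Analysis variable** (Data collection methods): "The analysis criterion for all variables will be the change from baseline values".
- **Baseline adjustment** (Statistical methods): "if clinically meaningful baseline imbalance is observed, ANCOVA models adjusting for baseline values will be performed as sensitivity analyses". No size of imbalance is given that would set this off. Linear mixed models are to be considered as a further sensitivity analysis for missing data. A meaningful disagreement between the supplementary analyses and the primary ANOVA is to be reported and discussed.
- **Planning correlation** (Sample size): "an assumed correlation of r = 0.5 between repeated measures". The calculation uses f = 0.48 from a partial η² of 0.19, and "Based on a significance level (α) of 0.05, statistical power (1-β) of 0.95". It gives a minimum of 18, with 30 to be enrolled and 20% attrition expected.

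**The concern.** The trial measures every outcome at baseline, but its primary test uses that value only by subtraction. Subtraction fixes the coefficient of baseline at 1. ANCOVA estimates it, and under randomisation this is at least as precise in large samples whatever the pre-post correlation. With at most 15 athletes per arm, that precision is worth having.

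The second issue is the trigger. Some chance baseline difference is to be expected at this size, and the change score over-corrects for it. The adjusted estimate would show this, but it is produced only if someone looks at the baseline table and judges the gap clinically meaningful, a term the plan does not define.

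At stake are the width of the confidence interval, some power if the true effect is smaller than planned, and whether readers see an adjusted estimate at all.

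**Working it through.** **Inputs.** From the protocol: two arms at 1:1, two times, r = 0.5, f = 0.48, two-sided α = 0.05, 30 enrolled, 20% attrition (30 × 0.8 = 24 completers). Assumed here: equal pre and post variances σ², and an alternative effect of 0.97 SD of change (explained below).

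**1. The plan's own figure.** f = √(0.19/0.81) = 0.484, in line with the stated 0.48. With the G*Power default scaling, λ = f² × N × 2/(1 − r) on (1, N − 2) degrees of freedom:
- N = 16: power 0.946
- N = 18: λ = 0.2304 × 18 × 4 = 16.59, power 0.968

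The stated minimum of 18 is reproduced.

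**2. Equivalence.** With two arms and two times, the interaction contrast is the difference between arms in mean change, so F(1, N − 2) = t² from a t-test on change. The primary test and the change-from-baseline sentence therefore describe the same analysis.

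**3. Variance.**
- Change score: 2(1 − r)σ² × 4/N
- ANCOVA: (1 − r²)σ² × (4/N) × [1 + 1/(N − 4)], where the bracket is the cost of estimating the slope
- Ratio: [(1 + r)/2] × [1 + 1/(N − 4)]

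| r | Large sample | N = 24 | N = 30 |
|---|---|---|---|
| 0.3 | 0.65 | 0.68 | 0.68 |
| 0.5 | 0.75 | 0.79 | 0.78 |
| 0.7 | 0.85 | 0.89 | 0.88 |
| 0.8 | 0.90 | 0.95 | 0.94 |

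At r = 0.5 and N = 24, for example: 0.75 × (1 + 1/20) = 0.788. Simulation with 20,000 trials per setting gave 0.78 at both sizes. The variance reduction at r = 0.5 is thus 21-22%. Since √0.788 = 0.89, the confidence interval is about 11% narrower.

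**4. Power at r = 0.5.** Noncentral t is used. The change score has N − 2 degrees of freedom and noncentrality d√(N/4), where d is the effect in SDs of change. ANCOVA has N − 3, with noncentrality divided by the square root of the ratio above.

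| Effect | N | Change score | ANCOVA |
|---|---|---|---|
| Plan's f = 0.48 (d = 4f = 1.92) | 18 | 0.968 | 0.989 |
| | 24 | 0.994 | 0.999 |
| | 30 | 0.999 | >0.999 |
| Assumed d = 0.97 | 24 | 0.62 | 0.72 |
| | 30 | 0.73 | 0.83 |

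The value d = 0.97 is 2 × √(0.19/0.81). It is what the same partial η² means if it is ordinary ANOVA output that already reflects the pre-post correlation. The protocol does not say which reading applies. For d = 0.97 at N = 24, ANCOVA power is 0.78 at r = 0.3, 0.67 at r = 0.7 and 0.64 at r = 0.8, each against 0.62.

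**5. Chance imbalance.** The standard deviation of the baseline difference at 15 per arm is √(2/15) = 0.37σ. Given a gap g, the expected change-score estimate is displaced by (1 − r)g in size. At r = 0.5 and g = 0.37σ this is 0.18σ, and the arm that starts higher appears to fall more. Averaged over randomisations the displacement is zero.

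**The case against.** The best defence is that nothing here is an error. The primary test is named in advance, matches the method used for the sample size, and is unbiased over randomisation. On the plan's own f = 0.48 its power is already 0.97 or more, so ANCOVA adds about 2 points at 18 participants and under 1 point at 24. All of that stands, and it makes this an efficiency recommendation.

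Four stronger readings are tempting but not supported:

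- **That the data choose the primary model.** They do not. ANCOVA is labelled a sensitivity analysis and cannot replace the ANOVA. Only the production of an extra analysis is conditional, and a meaningful discrepancy is to be disclosed.
- **That the change score is biased.** It is biased only conditionally on an observed gap. The 0.18σ is not a second loss on top of the variance loss: its spread over randomisations is already part of the change-score standard error.
- **That selecting athletes on high valgus widens ANCOVA's advantage.** Entry does require it: "DKV will be defined as a peak knee valgus angle greater than 12 degrees during the single-leg landing task". But selection also shrinks the baseline variance, so the equal-variance ratio no longer applies. In simulations keeping the top 30% on screening, with an unselected r of 0.5, the large-sample ratio ran from 0.92 to 0.70, against 0.75 unselected, depending on how closely screening tracks baseline. The protocol does not give that correlation, so the direction is unknown.
- **That a full quarter of the precision is lost.** That is the large-sample figure. It is 21-22% here, and less if r exceeds 0.5.

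**Conclusion.** The concern holds as a matter of efficiency and reporting. The plan fixes a valid primary test that is less precise than one available from data already being collected. It leaves the better-adjusted estimate to an undefined judgement about imbalance.

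At the plan's r = 0.5, ANCOVA lowers the variance by about 21-22% with 24 to 30 completers. At 24 completers the range is about 32% at r = 0.3 to 11% at r = 0.7, assuming equal pre and post variances. The narrower interval does not depend on the effect size. The power gain does: it is negligible at f = 0.48 and about 10 points at 0.97 SD of change. The smaller effect is an assumption, though a reasonable one to guard against, because the control arm performs the same exercises. The change should be made, but the planned analysis is not invalid without it.

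**What to change.** 1. In Statistical methods, make the primary analysis a linear model of the post-test value on arm and baseline value, fitted without condition. Report the adjusted mean difference in degrees with its 95% confidence interval. Use the same model for the continuous secondary outcomes, in their own units.
2. Keep the group × time repeated-measures ANOVA as a sensitivity analysis.
3. Delete the clause that makes ANCOVA depend on observed imbalance.
4. Reword the sentence in Data collection methods that sets change from baseline as the criterion for all variables, so that it agrees with the new primary model.

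The cost is wording and one residual degree of freedom (N − 3 in place of N − 2). The baseline values are already collected, and SPSS, the planned software, fits the model.

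### The primary pre/post ANOVA can use only athletes with both visits, while the missing-at-random mixed model is merely considered; if baseline-related loss differs between arms, the primary contrast is biased

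*Protocol article*

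**What the plan says.** Protocol article, Statistical methods, fixes the primary analysis: "Repeated-measures ANOVA will be used to evaluate the group × time interaction effect as the primary indicator of intervention effectiveness", with the factors given as "training vs. control; pre-test vs. post-test". The same section leaves the alternative open: "linear mixed models with appropriate covariance structures will be considered as sensitivity analyses to evaluate robustness under missing-at-random assumptions". It makes a baseline-adjusted ANCOVA a sensitivity analysis too, run only if a clinically meaningful baseline imbalance is seen. It promises to assess missing-data patterns, and to report and discuss any meaningful discrepancy between the supplementary analyses and the primary ANOVA.

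The Sample size section enrols 30 athletes, allowing for "an estimated 20% attrition rate". The article does not say in words that only complete pairs are analysed. That follows from the chosen method.

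**The concern.** With two visits, the group × time F test is the same test as a two-sample t test on change. An athlete without a post-test has no change score and drops out, together with her baseline. The result is then unbiased only if mean change among those lost would have differed from mean change among those kept by the same amount in each arm.

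A mixed model fitted by likelihood needs a weaker condition: loss may depend on arm and on baseline. The plan names that model but commits neither to running it nor to giving it weight. The headline p-value therefore rests on the stronger assumption. The arms differ by design in cognitive load, and the Background says cognitive challenge may worsen dynamic knee valgus. It is thus conceivable that baseline valgus is related to staying in the programme more strongly in one arm than in the other.

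**Working it through.** **Inputs from the Sample size section.** f = 0.48 (from partial η² = 0.19), "an assumed correlation of r = 0.5 between repeated measures", α = 0.05, power 0.95, minimum N = 18, 30 enrolled 1:1, 20% attrition.

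**Inputs assumed.** Normal baselines, 20% loss in each arm, and the dropout patterns in the table below.

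**1. The plan's own figure.** Noncentral F with λ = f²·N·m/(1 − r), m = 2 visits, df = (1, N − 2).
- N = 16: λ = 0.2304 × 16 × 2/0.5 = 14.75, power 0.946.
- N = 18: λ = 16.59, power 0.968.

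So 18 is the smallest even N that reaches 0.95, and the figure reproduces. Allowing for loss, 18/0.80 = 22.5, so 23 (24 for equal arms). Thirty enrolled less 20% leaves 24, where λ = 22.12 and power is 0.994. Complete-pair analysis therefore costs no planned power; the issue is bias.

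**2. Effect implied by that calculation.** In a 2 × 2 layout, a between-arm difference in change of D gives interaction effects of ±D/4, so f = D/(4 SD). Hence D = 4 × 0.48 = 1.92 SD.

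**3. Bias formula.** If loss depends only on arm and baseline, the bias of the complete-pair contrast is −(1 − r) × (difference between arms in mean baseline among completers). If one arm loses exactly its top fifth and the other loses at random, the completers' mean baseline in the first arm is −φ(0.842)/0.80 = −0.280/0.80 = −0.35 SD. The bias is 0.5 × 0.35 = 0.175 SD. If the arms lose opposite fifths, it is 0.5 × 0.70 = 0.35 SD. If both arms lose the same end, the two means cancel and the bias is 0.

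**4. Simulation.** 15 per arm, an expected 20% lost per arm, r = 0.5, no true effect, 20,000 trials per pattern. Log-odds of loss are per baseline SD.

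| Pattern of loss | ANOVA bias (SD) | ANOVA type I error | Mixed-model bias (SD) |
|---|---|---|---|
| Unrelated to baseline | 0.00 | 4.9% | 0.00 |
| Same in both arms (log-odds 2) | 0.00 | 5.0% | 0.00 |
| One arm only (log-odds 1) | 0.08 | 5.4% | 0.00 |
| One arm only (log-odds 2) | 0.13 | 6.4% | 0.00 |
| One arm loses its top fifth | 0.17 | 7.0% | 0.00 |
| Opposite in the two arms (log-odds 2) | 0.26 | 9.6% | 0.00 |
| Arms lose opposite fifths | 0.35 | 13.8% | 0.00 |

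With exactly three athletes lost per arm, the strict one-arm case gives 0.16 SD and 7.0%. Opposite ends give about 0.22 SD under partial dependence and 0.33 SD with about 13% type I error in the strict case.

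**5. Size against the planned effect.** 0.17/1.92 = 9%; 0.33/1.92 = 17%. With 12 completers per arm, the SD of change at r = 0.5 equals one baseline SD, so the standard error is √(1/12 + 1/12) = 0.408 SD. Noncentrality falls from 1.92/0.408 = 4.70 to (1.92 − 0.17)/0.408 = 4.29, and power from 0.994 to 0.984.

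**6. Precision.** With loss unrelated to baseline, the empirical SD of the estimate is 0.401 (mixed model) against 0.410 (complete pairs). The variance ratio is 0.401²/0.410² = 0.957, a gain of about 4%.

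**The case against.** **Bias is not automatic.** A reader might infer that any baseline-related dropout biases the primary answer. It does not: with a constant effect, loss related to baseline equally in both arms leaves the interaction unbiased (second row of the table). This stands.

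**Differential loss is assumed.** No section gives a dropout pattern. Both arms do the same exercises in the same session structure, athletes who do not meet progression criteria stay at their level with modified exercises, and reminders and makeup sessions are planned. This stands, and it makes the sizes conditional.

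**Larger percentages are tempting.** Reading the effect as 2f, about 0.97 SD, makes the one-arm bias about 17% of the effect and takes power from 63% to 49%. The plan's N = 18 does not reproduce on that scale, so those figures do not describe this plan's own calculation.

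**Direction.** If the experimental arm loses its highest-valgus athletes, the bias is towards no benefit. It favours the experimental arm only if the control arm loses them. A false benefit is one possibility, not the expected result.

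**Partly handled already.** Discrepancies are to be reported, and an ANCOVA on completers would remove the same bias. But the ANCOVA depends on an observed imbalance, the mixed model need not be run at all, and a discrepancy can be reported only from an analysis that was done.

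**The mixed model is no cure-all.** Its zero bias follows from simulating only loss that depends on arm and baseline. Loss driven by injury or poor response during training, and not explained by the recorded data, could bias both methods.

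**Conclusion.** The point holds in conditional form. The plan fixes as primary a method that needs complete pairs and a stronger missing-data assumption than the method it names as an optional check. If baseline-related loss differs between arms, the bias is about 0.1 SD (partial, one arm), 0.17 SD (one arm's top fifth) or 0.22 to 0.33 SD (opposite ends), with type I error about 6% to 13%. If the relation is the same in both arms and the effect is constant, there is no bias.

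These sizes rest on 20% loss per arm, r = 0.5, normal baselines and dropout patterns that the article does not supply. The documents do not show that the primary result will be biased, nor that the trial will lose meaningful power. The case for change is that the better method is already named, costs nothing when data are complete, and has to be chosen before outcomes are seen.

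**What to change.** In Statistical methods, make the primary analysis a linear mixed model on all randomised athletes in their assigned arm. Use both visits as outcomes, an unstructured 2 × 2 covariance, the arm × time term as the test, and small-sample degrees of freedom. Keep the complete-pair repeated-measures ANOVA as the sensitivity analysis, and replace the wording that mixed models will be considered with a commitment to run them. Keep the baselines of athletes who withdraw in the dataset, since the model helps only if they are used.

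The cost is two sentences. SPSS version 27, the plan's software, fits the model. With no missing visit the result is the same as the ANOVA's, and the sample size does not change.
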